**Overall Analysis Plan**

The objectives of this aim are (1) to examine the affective attributes (percentage pro/con/neutral) of online newspaper articles writing about the South African SSB tax and whether these change from before to after the tax; (2) examine reasons given for excessive sugar consumption and obesity and whether these causes differ by whether the article is pro, con, or neutral toward the tax; and (3) to test whether pro and con framed articles differ in their proposed solutions to reducing SSB intake (e.g. better education as individual level solution versus taxes as government policy solutions). This analysis will help identify the arguments that are used by either support for or against the SSB tax, which will inform future policymaking.

**Sample Selection**

*Search strategy*

Adapting methods that have been previously described^62,98^, we will conduct a systematic analysis of online news article coverage of the April 2018 SSB tax (called the Health Promotion Levy), using two databases: (1) Nexus Uni, a global database that provides access to full text news, business and legal articles and (2) Google News, a global news aggregator search engine. After our initial searches in these two databases, we will manually search for any potentially missing articles from the top South African newspaper sites listed by Stanford libraries^99^. We will search for articles containing the terms (“tax” OR “levy” OR “health” OR “health promotion”) AND one or more of the following terms: “beverage”, “soft drink”, “soda”, “fizzy drink” AND at least one mention of “sugar”, “sugary”, “sweet”, or “sweetened” AND ("South Africa" OR Johannesburg OR Pretoria OR “Western Cape” OR “Cape Town”). Articles will be included in our search if they were published between October 1, 2017 (6 months before the tax) and October 1, 2019 (6 months after the tax) and were published in English. English is the primary language in South African education, journalism, broadcasting, and advertisements^101^, and news media readership is moderately high in South Africa; 17.5 million (50%) South Africans over the age of 15 read newspapers^102^. We will use the online software product Covidence, commonly used in systematic reviews, to streamline the article review process. Article headlines and abstracts will be read, and clearly irrelevant articles will be excluded.

*Coding*

Our unit of analysis will be the article. We will develop a coding instrument adapted from previous media content analysis work^63^ to assess the presence or absence of supportive (pro) and opposing (con) frames in news coverage about the SSB tax. Pro frames support the policy and argue for either reducing SSB consumption or improving health. Con frames oppose the policy and argue that the SSB tax is regressive (harmful to the poor), harmful to business, or otherwise unfair to certain groups. Articles will be coded as pro, con, or neutral. Neutral articles are either entirely factual or contain both positive and negative frames in equal amounts (>40% of either). To achieve acceptable intercoder reliability, articles will be read by the lead coder and a random 20% subsample will be read and coded by a colleague to ensure intercoder reliability of article content. We will use Krippendorff’s α of 0.8 as a threshold for high agreement^103^.

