South Africa, with one of the highest SSB consumption rates in Africa and a growing burden of type II diabetes^12^, is the first sub-Saharan African country to institute a sugary beverage tax, implemented in April 2018. They have introduced a novel tax structure that taxes each additional gram of sugar above a 4g/100 ml threshold^13^. Such an approach has not been tried nor tested anywhere. **The purpose of this proposal is to examine changes in SSB intake, SSB knowledge, and media coverage that occur in response to this SSB tax, which could serve as a model for future SSB tax evaluations.** Our specific aims are to:

**Aim 1: Estimate the pre-post changes in SSB dietary intake in South Africa.** To evaluate the South African 4g/100 ml threshold SSB tax policy, we will analyze 24-hour dietary recalls and beverage frequency intake data from the Langa 18-39y Survey of young township adults (n=2383) from Cape Town, South Africa. These data were collected at baseline (March 2018, 1 month prior to tax implementation), 6 months after, and 12 months after tax implementation. *Based on results from Mexico and Chile evaluations,* *we hypothesize that* *taxed* *SSB consumption by 18-39 year-olds living in Langa will decrease by 6% at 12 months.*

**Aim 2:** **Examine changes in tax awareness, SSB knowledge, and SSB risk perception, and determine whether these variables modify the relationship between SSB consumption and time since tax implementation.** We have collected data on participants’ awareness of the tax, knowledge about SSBs, and risk perceptions for developing obesity, diabetes, and high blood pressure as a consequence of high SSB intake. These data were collected at baseline, 6 months after, and 12 months after tax implementation. We will test whether there were changes in tax awareness, SSB knowledge, or SSB risk perception. We will then test whether there is an interaction between time and awareness, knowledge, and perceptions on SSB intake. *Our hypothesis is there will be a significant interaction between time of data collection and knowledge, such that a higher knowledge about health risks will be associated with reductions in SSB intake, and this relationship will be stronger after the tax. We expect to see similar effect modification for the other two modifiers.*

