**Aim 3: Examine framing of newsprint articles related to the South African SSB tax, whether framing changes over time, and whether framing is associated with proposed causes and solutions for excessive SSB intake.** To understand public discourse around the SSB tax implementation, we will perform a quantitative media content analysis of online newspapers in South Africa for six months preceding and following the SSB tax implementation. We will examine the media response to the tax according to the framing of the relationship between SSBs and health outcomes, assignment of responsibility (i.e. individual or industry), and proposed solutions (individual behavior or policy). We will also examine whether media framings change over time. *We hypothesize that framing excessive SSB consumption as a public health problem is associated with positive messaging and tax support, and framing SSB consumption as an individual problem is associated with arguments against SSB taxation.*

1. **Significance**

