**Aim 3: Examine framing of newsprint articles related to the South African SSB tax, whether framing changes over time, and whether framing is associated with proposed causes and solutions for excessive SSB intake.** Beyond their potential impacts on public health, SSB taxes are subject to policy and ethical arguments both in academia^31,92–97^ and in the media^53,62,98^. Media representations of public health policies have a strong effect on public opinion and therefore can affect the likelihood of success or failure of policy proposals^33,55,69^. Media coverage may also increase public awareness of the tax, as we are testing in Aim 2. In this study, we will analyze the response to the SSB tax before and after its implementation in April 2018 to inform SSB policy advocacy in South Africa and across the region. We will perform a quantitative media content analysis of the twenty most widely read English-language online newspapers^99^ across multiple news genres in South Africa for six months preceding and following the SSB tax implementation. We will examine the media response to the tax by coding articles according to the affective attributes (positive, negative, or neutral) and the substantive attributes such as framing of the relationship between SSBs and health outcomes, assignment of responsibility (i.e. individual or industry), and proposed solutions (individual behavior or policy)^100^. We will also examine whether those articles that characterize the problem with excess sugary beverage consumption and weight gain as an individual problem are more likely to propose individualized solutions rather than public health policy solutions.

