**Statistical testing**

First, we will conduct a descriptive analysis of the articles obtained in our search according to whether they are for supporting the tax, against the taxed, or mixed (Table 5). Next, we will conduct proportions testing to test whether there are significant differences in the percentage of positive and negative articles in the time periods before versus after the South African SSB tax.

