**Timeline**

**Table 8. Projected Timeline for Completion of Study Aims**

|  | **2019** | | | | **2020** | |
| --- | --- | --- | --- | --- | --- | --- |
|  | **Q1** | **Q2** | **Q3** | **Q4** | **Q1** | **Q2** |
| **Proposal preparation** |  |  |  |  |  |  |
| **Data Collection and Cleaning** |  |  |  |  |  |  |
| **Aim 1** |  |  |  |  |  |  |
| Analysis using 0, 6, and 12 Month Data |  |  |  |  |  |  |
| **Aim 2** |  |  |  |  |  |  |
| Analysis using 0, 6, and 12 Month Data |  |  |  |  |  |  |
| **Aim 3** |  |  |  |  |  |  |
| Data 6 months prior and following April 2018 |  |  |  |  |  |  |

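### Aim 3's media search closes on October 1, 2019, labelled six months after an April 2018 tax, but that date is about 18 months after it

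*Protocol*

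**What the plan says.** The search strategy under Sample Selection in Aim 3 is the only place where the media search has calendar dates. It admits English-language articles published between "October 1, 2017 (6 months before the tax) and October 1, 2019 (6 months after the tax").

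The date of the tax is not in doubt. The Specific aims say that South Africa "is the first sub-Saharan African country to institute a sugary beverage tax, implemented in April 2018", and the Aim 3 introduction says "we will analyze the response to the SSB tax before and after its implementation in April 2018".

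Three other places give the intended window:
- Specific aims, Aim 3: "online newspapers in South Africa for six months preceding and following the SSB tax implementation".
- Aim 3 introduction: "in South Africa for six months preceding and following the SSB tax implementation".
- Table 8, the timeline: "Data 6 months prior and following April 2018".

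The window feeds the analyses. The Outcomes section of Aim 3 takes the number of pro, con and neutral articles as the key outcome. Statistical testing then looks for "significant differences in the percentage of positive and negative articles in the time periods before versus after the South African SSB tax". The cause and solution cross-tabulations (Tables 6 and 7) have no stated restriction by period.

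**The concern.** The closing date and its label cannot both be right. The date is what a searcher would enter into the databases, whereas the label and three other statements describe a different window. Two analysts could each follow the protocol faithfully, one by the date and one by the label, and assemble different sets of articles.

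If the date is followed, an extra year of coverage enters the post-tax counts, the before-after comparison of percentages and the pooled cause and solution tables. If the conflict is noticed only after articles have been coded, the window will be chosen after the data have been seen, in an aim that tests stated hypotheses.

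**Working it through.** **Inputs**
- Search opens October 1, 2017 and closes October 1, 2019 (Aim 3, search strategy).
- Tax in April 2018, with no day given (Specific aims; Aim 3 introduction). The label on the opening date implies about April 1, which is used here. April 30 is used as the other extreme.

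**Opening label**
- October 1, 2017 to April 1, 2018 is 3 + 3 = 6 months (182 days). The stated six months is reproduced.

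**Closing label**
- April 1, 2018 to October 1, 2019 is 12 + 6 = 18 months (548 days). The stated six months is not reproduced.
- With April 30, 2018 as the tax date, the interval is still about 17.05 months. No day in April 2018 rescues the label.

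**Shape of the window as written**
- Total: 6 + 18 = 24 months.
- Post-tax share of calendar time: 18/24 = 75%. With six months on each side it would be 6/12 = 50%.
- Post-tax months outside the intended frame: 18 − 6 = 12, or 12/18 = 67% of post-tax calendar time.

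These are shares of months. The unit of analysis is the article, and the protocol gives no article rates, so they are not shares of articles.

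**Effect on counts**
- A count over 18 months includes everything in its first 6 months and can only be equal or larger. As an illustration, assume a constant rate of r articles per month throughout. The expected counts are then 6r before and 18r after, a threefold difference with no change in coverage.

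**Effect on percentages**
- Let p_early be the share of con articles in the first 6 post-tax months, p_late the share in the next 12, and w the fraction of post-tax articles that fall in those 12 months. The post-tax share under the literal rule is (1 − w)·p_early + w·p_late. It differs from the intended one by w·(p_late − p_early).
- The protocol gives none of these quantities. In principle w can lie anywhere between 0 and 1. It is 12/18 = 0.67 under a constant rate, and lower if coverage peaks in April 2018 as the Expected Results anticipate. The sign of p_late − p_early is unknown. Neither the size nor the direction of the shift can be derived.

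**With the date corrected**
- April 1 to October 1, 2018 is 6 months (183 days), against 182 days before the tax, for a 12-month total.

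**The case against.** The strongest reply is that this is a slip of one digit in the year. The wrong date carries its own label, and three other statements agree with the label, so the team would probably notice. That is a fair account of how the error arose. It does not remove the need for a correction, because the wrong figure sits in the operative inclusion rule and no other calendar dates are given for the search.

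A second reply is that the planned time comparison concerns percentages, and a test of proportions does not need periods of equal length. This stands. A reader might infer that the 1:3 split invalidates the test, but it does not. What changes is which period the post-tax percentage describes.

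A reader might also infer that the longer window dilutes a predicted surge of opposing articles around April 2018. The protocol predicts no such surge. Its Expected Results anticipate a peak in total coverage in April 2018 and a higher percentage of anti-tax articles after the tax. The surge of opposition that it mentions, under Media Response Impact, belongs to a cited analysis of United Kingdom coverage. The literal post-tax window also still contains the launch period, and dilution would require article rates that the protocol does not give.

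Finally, running about six months past the 12-month survey wave carries little weight. The Aim 3 limitations say that media exposure was not measured in the survey population, so the media results are descriptive context and are not linked to respondents.

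**Conclusion.** The closing date is wrong as written. It is about 18 months after the tax (17 to 18 for any day in April 2018), against a label and three other statements of six. Taken literally, the search covers 6 pre-tax and 18 post-tax months and admits 12 months outside the study's own frame. Post-tax counts would be inflated. The before-after percentages and the pooled cause and solution tables may shift, but how far and which way cannot be estimated from the protocol.

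Only one of the three Aim 3 objectives is a before-after comparison. For the other two, the longer window changes the sample without creating an imbalance between periods. Aims 1 and 2, including the intake outcomes, are untouched. The conclusion rests on the April 2018 tax date and on the six-month window being the intended one, which the protocol states consistently everywhere else.

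**What to change.** In the Aim 3 search strategy, change the closing date to October 1, 2018 before the search is run. This restores six months on each side of April 1, 2018 and brings the rule into line with the Specific aims, the Aim 3 introduction and Table 8. If later coverage is of interest, report it as a separately labelled extension, outside the before-after test and not pooled into the main tables. The cost is one date, and there are fewer articles to screen and code.

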**Outcomes**

Our key outcomes for this analysis will be the number of pro, con, or neutral articles. We will analyze whether the distribution of these key outcomes differs by time period, proposed cause of high SSB consumption and proposed solution.

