**Table 5. Framing of news documents covering the South African SSB tax before and after it was passed in April 2018**

| **Source** | **Pro (%)** | **Con (%)** | **Mixed (%)** |
| --- | --- | --- | --- |
| *Pre-tax period total* |  |  |  |
| Source 1 (n = X) |  |  |  |
| Source 2 (n = X) |  |  |  |
| *Post-tax period total* |  |  |  |
| Source 1 (n = X) |  |  |  |
| Source 2 (n = X) |  |  |  |

Next, we will measure the prevalence of different explanations for the cause of excessive SSB consumption and intake of added sugars, following the methods of Buckton and colleagues^62^ (Table 6). We will categorize articles into one of five broad categories: relating to the role of individual decision making for health, the role of industry, the role of society and cultural norms, the role of the government, and the role of scientists (Table 6). Next, we will examine whether these different explanations are associated with support for the tax. We will perform cross-tabulation chi-squared testing to determine whether the percentage of articles supporting the tax differs by the category of cause identified (Table 6).

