**Table 6. Frequency of mentioning potential drivers of high SSB consumption and excessive intake from added sugars**

| **Cause** | **n (%)** | **Pro (%)** | **Con (%)** | **Mixed (%)** |
| --- | --- | --- | --- | --- |
| ***Failure of the individual*** |  |  |  |  |
| Individual predisposition (biological, genetic, or psychological) |  |  |  |  |
| Personal choice |  |  |  |  |
| Family background |  |  |  |  |
| Parenting decisions |  |  |  |  |
| Individual dietary habits |  |  |  |  |
| ***Failure of Industry*** |  |  |  |  |
| Inadequate self-regulation of industry and lobbying |  |  |  |  |
| Production and sales of unhealthy products |  |  |  |  |
| Advertising and marketing |  |  |  |  |
| product pricing and pricing promotions |  |  |  |  |
| Insufficient healthy alternatives at restaurants |  |  |  |  |
| ***Failure of society*** |  |  |  |  |
| Geographic areas with few healthy options/abundant fast food |  |  |  |  |
| Entrenched tastes preferences for sweets |  |  |  |  |
| Schools do not provide sufficient nutrition education |  |  |  |  |
| ***Failure of government*** |  |  |  |  |
| Public health education is insufficient |  |  |  |  |
| Unhealthy food environment |  |  |  |  |
| Insufficient regulation or fiscal pressure on industry |  |  |  |  |
| Political behavior |  |  |  |  |
| ***Failure of science*** |  |  |  |  |
| Industry influence on nutrition research |  |  |  |  |
| Problematizing scientific consensus on link between sugar and poor health |  |  |  |  |

Finally, we are interested in whether the pro and con articles differ by the proposed solutions suggested in the articles (Table 7). We will perform cross-tabulation chi-squared testing to determine whether the percentage of articles supporting the tax differs by category of proposed solutions (Table 7).

**Table 7. Analysis plan testing whether there are significant differences between the number of pro and con articles for each proposed solution**

| **Proposed solutions** | **Pro *** | **Con*** |
| --- | --- | --- |
| Individual responsibility | ↓ | ↑ |
| Industry voluntary action | ↑ | ↓ |
| Societal responsibility and changing norms | ↑ | ↓ |
| Government regulation | ↑ | ↓ |
| Role of scientists | ↓ | ↑ |

*Pro and con indicate whether the article is either in favor or against the tax. Arrows indicate predictions for whether pro or con arguments will be more prevalent.

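### Aim 3 tests articles as if independent, with no rule for reprinted text and no analysis by outlet, so its type I error exceeds nominal under identifiable conditions and a change in outlet mix can look like a change in framing

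*Protocol*

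**What the plan says.** The opening paragraph of Aim 3 announces a "quantitative media content analysis of the twenty most widely read English-language online newspapers". Under Search strategy, articles are found through a full-text news database, "Google News, a global news aggregator search engine", and a manual check of newspaper sites. Date, language and relevance decide inclusion. Nothing is said about the same text appearing in more than one outlet.

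Under Coding, "Our unit of analysis will be the article". Under Outcomes, "Our key outcomes for this analysis will be the number of pro, con, or neutral articles". Three tests follow:

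- Before versus after: "we will conduct proportions testing to test whether there are significant differences in the percentage of positive and negative articles in the time periods" before and after the tax, pooled over outlets.
- Stance by cause: "We will perform cross-tabulation chi-squared testing to determine whether the percentage of articles supporting the tax differs by the category of cause identified", with five broad cause categories.
- Stance by solution: a chi-squared test of whether the "percentage of articles supporting the tax differs by category of proposed solutions", with five solution categories in Table 7.

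Outlet appears only as the rows of Table 5, which is descriptive. The Aim 3 Limitations discuss causal claims, lack of exposure data, English-only sources and the time window, but not reprints, clustering or outlet mix.

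**The concern.** A proportions test or a chi-squared test takes each article as a separate, independent piece of evidence. Two features of the sampling can break this.

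First, a story carried by several outlets enters once per outlet with the same stance, cause and solution. Removing duplicate database records would not remove it, because each printing is a separate record. Second, an outlet's editorial line can make its articles resemble one another.

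A different problem, of interpretation rather than error rate, affects the before/after test. Because it pools outlets, the percentage can change when outlets contribute different shares of the articles in the two periods.

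These tests decide stated expectations: that framing goes with support for the tax, and that the share of anti-tax articles rises significantly after it. The Overall Analysis Plan says the results are meant to inform policymaking. The protocol itself fixes both the unit and the tests, so this is not detail left for a statistical analysis plan.

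**Working it through.** The protocol gives no article count, power, error rate, reprint share or within-outlet correlation for Aim 3, so there is no stated figure to reproduce. The only alpha in the document is 0.1, in the Study Power section for Aim 1. The checks below assume a nominal two-sided 5%.

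**1. Reprints.** Let a share s of distinct texts run k times each and the rest once. All copies carry the same codes and, for the before/after test, are taken to fall in the same period. The variance of the counts is inflated by

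deff = [(1 − s) + s·k²] / [(1 − s) + s·k].

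The actual error is 2·[1 − Φ(1.96/√deff)] on 1 df. On 4 df (five causes by supports/does not support) it is P(χ²₄ > 9.488/deff) = e^(−c/2)·(1 + c/2), with c = 9.488/deff.

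Worked case, s = 0.10 and k = 3:

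- deff = (0.90 + 0.90)/(0.90 + 0.30) = 1.50.
- 1 df: 1.96/√1.50 = 1.600, so the error is 0.110.
- 4 df: c = 6.325, and e^(−3.163) × 4.163 = 0.176.

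| Assumed share reprinted | Times run | deff | Error, 1 df | Error, 4 df |
|---|---|---|---|---|
| 10% | 2 | 1.18 | 7.1% | 9.1% |
| 20% | 2 | 1.33 | 9.0% | 13.0% |
| 10% | 3 | 1.50 | 11.0% | 17.6% |
| 20% | 3 | 1.86 | 15.0% | 27.6% |
| 30% | 3 | 2.125 | 17.9% | 34.7% |

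Simulation with 150 distinct texts and no true association agrees to about one percentage point: 12% and 17% for 10% run three times, 9% and 12% for 20% run twice, and 18% and 35% for 30% run three times.

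**2. Outlet clustering without reprints.** Simulation with 20,000 data sets per scenario used 20 outlets of unequal size, 200 or 400 articles (split equally between periods for the before/after test), a true share of 40%, and beta-distributed outlet shares. The intra-outlet correlation (ICC) ran from 0.02 to 0.20, or from 0.05 to 0.20 in the last row. All tests are 2×2 (1 df).

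| Situation | Error, 200 articles | Error, 400 articles |
|---|---|---|
| Before/after; slant and mix stable | 4.9–5.3% | 4.7–5.0% |
| Before/after; slant redrawn independently in each period | 7–23% | 8–34% |
| Before/after; slant stable, outlet sizes reshuffled | 6–12% | 6–18% |
| Stance by cause; both vary by outlet, unrelated within outlet | 5–11% | 6–17% |

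The first row matters most for wording: when slant and mix are both stable, the before/after test is not distorted.

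**3. Outlet mix.** Assume two outlet groups with fixed con shares of 20% and 60%, and let the second group's share of articles move from 40% to 60%.

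- Before: 0.6 × 20% + 0.4 × 60% = 36%.
- After: 0.4 × 20% + 0.6 × 60% = 44%.

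The pooled con share rises 8 points although neither group changed. The planned test would call this significant about 21% of the time with 100 articles per period, 37% with 200 and 52% with 300. More articles make the result more likely to mislead if it is read as a change of framing within outlets.

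**The case against.** The strongest reply has four parts.

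- **No reprinting is documented.** The protocol nowhere says that texts are syndicated. That is inferred from searching a full-text database, an aggregator and newspaper sites without a reprint rule. A reader might infer that the planned tests reject far too often. The documents do not support that: with 10% of texts run twice, the 1 df test moves only from 5% to about 7%. This limit stands.
- **Clustering alone need not matter.** A reader might infer that drawing articles from about twenty outlets makes every test invalid. It does not, as the stable-slant, stable-mix result shows. The number twenty itself rests on the Aim 3 opening paragraph; the Search strategy does not expressly confine the search to those papers. This stands too.
- **The pooled percentage may be the quantity wanted.** The Limitations describe the aim as describing change in the media landscape as a whole, and the outcome is a count of articles. On that purpose each printing is coverage, and a change in which outlets write about the levy is part of the finding. Table 5 would also show the mix by source and period. This stands for the descriptive counts. It does not rescue the independence assumption behind the p-values, and Table 5 displays outlet mix without adjusting for it.
- **Scope.** Aim 3 is associational, disclaims causal conclusions and does not touch the Aim 1 intake outcomes. That limits the importance of the point but does not remove it, since the protocol chose significance tests and attached expectations to them.

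**Conclusion.** The point holds in conditional form. As written, the plan counts reprinted and same-outlet articles as independent evidence and has no step to check or correct this. Type I error exceeds nominal if texts are reprinted, if outlet slant varies by period, if the outlet mix shifts while outlets differ in slant, or if stance and cause or solution both depend on outlet. The five-category tests suffer more from reprints than the before/after test. Every size given rests on assumed reprint shares, article counts and intra-outlet correlations, so none predicts the error rate of this study.

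Separately, the pooled before/after comparison cannot tell a change in framing within outlets from a change in which outlets published. That is not an error if landscape change is the target. It becomes one if the result is reported as outlets having changed their framing. The matter deserves correction, but it is confined to Aim 3.

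**What to change.** 1. Keep raw article counts, by source and period, as the description of coverage.
2. For the tests, link verbatim and near-verbatim reprints and count each text once, or cluster on text. Set the similarity rule before coding starts, because linking copies afterwards is harder.
3. Beside the pooled before/after test, add a comparison stratified by source (Mantel-Haenszel, or a model with outlet terms). Report the two as different quantities: change in the landscape, and change within outlets.
4. For stance by cause and stance by solution, use permutation within outlet, or outlet-clustered standard errors with a small-cluster correction. With about 20 unequal clusters, uncorrected clustered errors can themselves be too small. Collapse categories if cells are sparse.
5. Add reprints and outlet mix to the Aim 3 Limitations.

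The source is already needed for Table 5, so steps 3 and 4 cost a few lines of plan. The real cost is writing and applying the similarity rule, together with somewhat wider intervals.

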**Expected Results**

We expect that coverage peaked in April 2018 after the passing of the SSB tax, with a significantly greater percentage of anti-tax articles published after the tax as a reaction against it. These negative articles will be more likely to question the role of sugary beverages and added sugars as contributors to weight gain and poor health outcomes. These con articles will be more likely to suggest preferred individual level solutions such as making better choices and exercising more instead of policy solutions, which will be suggested to be economically unjust (e.g. loss of jobs or targeting the poor).

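### Aim 3: support for the tax overlaps by definition with one solution category and one cause item it is tested against, so the government part of the Table 6 and 7 tests can reject without a real association

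*Protocol*

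**What the plan says.** The coding paragraph (Aim 3, Sample Selection) defines the outcome partly by argument content. On one side, "Pro frames support the policy and argue for either reducing SSB consumption or improving health". An article on the other side rejects the levy and is expected to "argue that the SSB tax is regressive (harmful to the poor), harmful to business, or otherwise unfair to certain groups".

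Aim 3, Outcomes, makes the number of pro, con and neutral articles the key outcome: "We will analyze whether the distribution of these key outcomes differs by time period, proposed cause of high SSB consumption and proposed solution". For solutions, the chi-squared test asks "whether the percentage of articles supporting the tax differs by category of proposed solutions" (text introducing Table 7). A parallel test is planned for the causes in Table 6.

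The third objective (Aim 3, Overall Analysis Plan) illustrates the solution categories as "better education as individual level solution versus taxes as government policy solutions". Table 7 has a *Government regulation* row, predicted to be more common in pro articles. Its footnote defines pro and con simply as being for or against the tax.

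The hypothesis (Specific aims, Aim 3) has two halves. The first is that "framing excessive SSB consumption as a public health problem is associated with positive messaging and tax support". The second turns to personal responsibility and predicts that "framing SSB consumption as an individual problem is associated with arguments against SSB taxation". Expected Results adds that con articles will prefer individual solutions "instead of policy solutions, which will be suggested to be economically unjust (e.g. loss of jobs or targeting the poor".

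**The concern.** A test of association between two codes is informative only if an article can receive one without receiving the other as a matter of definition. Here the tax is both the object of the stance code and the named example of a government solution. Nothing in Aim 3 keeps support for the levy out of the *Government regulation* count. The same content can then be scored on both sides of the cross-tabulation, and the resulting association points the way Table 7 predicts.

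The planned reliability check would not reveal this. Krippendorff's α measures whether two coders agree, and two coders can agree perfectly on overlapping categories.

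At stake is the government side of the individual-versus-government contrast. Overall Analysis Plan says this analysis will inform policymaking.

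**Working it through.** The protocol gives no article count, significance level or effect size for Aim 3, so there is no figure to reproduce. The check first compares the definitions and then illustrates the size.

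**Step 1: where the definitions meet**

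| Element tested or expected | Shared with the stance code? |
|---|---|
| Table 7, *Government regulation* | Yes: taxes are the named example of a government solution |
| Table 7, other four rows (individual, industry voluntary action, society, scientists) | No: in neither definition |
| Table 6, third item under *Failure of government* | Yes: close to the case for the tax |
| Table 6, other 18 of 19 items (5 + 5 + 3 + 4 + 2 = 19) | Not fixed by the definitions |
| Public-health half of the hypothesis | Tilted: a health or SSB-reduction argument is part of the pro definition |
| Individual-problem half of the hypothesis | No |
| Expectation that con articles call policy economically unjust | Restates the con definition; no planned test |
| Before/after comparison of pro and con percentages | No: uses no cause or solution code |

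**Step 2: size for the government row**

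All inputs are assumptions:
- 200 pro or con articles, half of them pro;
- a government measure proposed at base rate b, unrelated to stance;
- a share f of pro articles also coded there only because they support the tax;
- a 2×2 chi-squared test without continuity correction at 0.05.

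The con rate is b and the pro rate is b + (1 − b)f.

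- b = 0.2, f = 0.10: 0.2 + 0.8 × 0.10 = 0.28 against 0.20
- b = 0.2, f = 0.25: 0.2 + 0.8 × 0.25 = 0.40 against 0.20
- b = 0.4, f = 0.10: 0.4 + 0.6 × 0.10 = 0.46 against 0.40
- b = 0.4, f = 0.25: 0.4 + 0.6 × 0.25 = 0.55 against 0.40

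Share of 1,500 simulated data sets in which the test rejects, with no true association:

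| f | b = 0.2 | b = 0.4 |
|---|---|---|
| 0 | 6.1% | 5.7% |
| 0.10 | 25% | 15% |
| 0.25 | 89% | 56% |
| 0.50 | 100% | 99% |
| 1 | 100% | 100% |

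Hand check for b = 0.2, f = 0.10, with 100 articles per group. The pooled rate is 0.24, the standard error is √(2 × 0.24 × 0.76/100) = 0.060, and z = 0.08/0.060 ≈ 1.3. The chance of exceeding 1.96 is then about 26%, in line with the simulated 25%.

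From 100 to 400 articles, f = 0.25 gives 34% to 99%. With f = 0 the rate is 3.9% to 6.1%, about nominal.

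**Step 3: a row outside the definitions**

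In the same simulations, an individual-responsibility code (base rate 30%, unrelated to stance) rejected in 4% to 6% of data sets at every overlap. The artefact stays in the overlapping row.

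**Step 4: the extreme case**

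Take 50 pro and 50 con articles. All pro articles count under *Government regulation* because they support the tax, and 15 of the con articles also count there. Then chi-squared = 100 × (50 × 35 − 0 × 15)² / (50 × 50 × 65 × 35) = 53.8. If 15 in each group propose some other government measure and the tax is left out, chi-squared is 0. This is an upper bound, because it sets the overlap at 100%.

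**The case against.** A reader might infer that the main Aim 3 associations are all true by construction and that the tests would confirm the hypotheses whatever the press wrote. The documents do not support that. Step 1 finds overlap in one of five solution rows and one of 19 cause items. The other Table 7 predictions can fail, and so can the individual-problem half of the hypothesis.

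Two further limits stand. No public-health-problem variable is tabulated, and the pro definition requires both support for the policy and the argument. A health-framed article that opposes the tax is therefore not pro, so the public-health half is tilted rather than settled. The economically-unjust expectation has no row in Table 6 or 7 and yields no p-value.

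It can also be said that the coding instrument is still to be developed, that no rule says support for an existing levy counts as a *proposed* solution, and that the Table 7 footnote already defines stance by position on the tax. These points limit how certain the overlap is and how large. They do not remove it: the protocol itself names taxes as a government solution, and the coding paragraph itself adds argument content to the stance definitions. Coding stance and content from the same article is normal practice; the fault is the shared definition.

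Finally, the Aim 3 Limitations disclaim causal claims and confine the work to associations between aspects of media content. That is fair, but an association produced by the coding misleads even as a description.

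**Conclusion.** The concern holds in a limited form. As defined, the government part of the Table 6 and 7 tests, and hence the tests across categories to which it contributes, can reject without any real association. For the *Government regulation* row with 200 articles, rejection is about 15–25% at 10% overlap and 56–89% at 25%, against about 5% with none.

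These figures rest on assumed article numbers, base rates, overlap and significance level. They describe a single row, not the full multi-category test, where the effect depends on the other rows as well. The true overlap cannot be known until the articles are coded.

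Separately, mixing position with argument in the stance definitions tilts the public-health half of the hypothesis and makes the economically-unjust expectation a restatement rather than a finding. This is worth correcting before coding because it changes what the solution and cause tests can show.

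**What to change.** 1. In the coding paragraph, define stance only by the article's position on the levy, in line with the Table 7 footnote. Remove the health argument from the pro definition and the regressivity, business-harm and unfairness arguments from the con definition.
2. Code health, equity and business arguments as separate items, so that their relation to stance is observed rather than defined.
3. When cross-tabulating with stance, run the Table 6 and 7 tests with the levy and calls for SSB fiscal pressure excluded from *Government regulation* and *Failure of government*. Report the version that includes the levy as descriptive only.

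The cost is a codebook and tabulation change before coding and slightly more coding work. Associations will probably look weaker, and the education-versus-tax contrast in the third objective becomes descriptive.
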